### Lung tissue and BALF

3.5

Only for group Pct-chir, BALF is sampled at inclusion to the study. This sample is taken as a part of patient's standard care protocol if decided by his/her physician, and is not taken as an additional sample for this study. The BAL is performed by routine bronchoscopy procedure.

Sampling of lung tissue and BALF during surgery is performed for both groups, after partial or complete pneumonectomy. The removed lung tissue is placed in a sterile vessel and the tumour position is determined by palpation. A piece of healthy lung distal to the tumour, with a minimum size of 1 cm × 1 cm × 1 cm, is then clamped. The clamp is left in place during the following procedure. The stich on the bronchus is cut away and using a sterile syringe the lung is inflated through the bronchus. Lavage is performed by instilling 2 × 40 mL of sterile physiological saline. After each instillation, the maximum amount of liquid inside the bronchus is retrieved (8–10 mL in total), poured into a sterile 50 mL tube and placed immediately on ice, designated as “BALF”. At the end, the clamped wedge is cut off and designated as “healthy lung”. A slice of the tumour, with a minimal weight of 400 mg, containing the tumour cross-section is excised along with peritumoural tissue, after which the 2 are separated based on histological difference. All tissues are frozen 1st in liquid nitrogen and then placed at −80°C for long-term storage until DNA extraction. The mirror piece of the excised tumour slice is stored in paraffin and later analysed by immunohistochemistry for characterisation of tumour infiltrate. A 3 mL of BALF are immediately used for immune cell analysis by flow cytometry and the remainder is stored at −80°C for later DNA extraction.

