### Study outcomes

2.2

As its primary outcome, this study will characterise the lung and UAs microbiota in 2 groups of 20 patients with NSCLC. Group Pchir will include patients eligible for surgery without chemotherapy. Group Pct-chir will include patients eligible for surgery after platinum-based chemotherapy. The UAs microbiota will be evaluated from saliva, while lung microbiota will be evaluated from 3 lung explants: “healthy” lung tissue, tumour and peritumoural tissue; and broncho-alveolar lavage fluid (BALF) from the tumour's proximity (same lobe). Following bacterial DNA extraction, microbiota will be analysed by qPCR and 16S ribosomal rRNA gene sequencing using the Illumina MiSeq platform.

Secondary outcomes of this study are set as follows:

i)to study the effect of neoadjuvant chemotherapy on microbiota by evaluating:a.the variation of the proportion of the phylum *Firmicutes* (as the phylum is highly represented in all of the different types of samples considered in this study),^[4]^b.the variation of the proportion of the bacterial genera per phylum in different types of samples (faeces, saliva, BALF, lung tissue/peritumoural tissue/tumour),c.the concordance of genera between sample locations (e.g. saliva vs. BALF, healthy lung tissue vs. peritumoural tissue vs. tumour);by qPCR and 16S rRNA gene sequencing;ii)to study the homogeneity/heterogeneity between lung, upper airways and gut microbiota for each and between both groups (evaluated by 16S rRNA gene sequencing and qPCR) and between different time points (group Pct-chir),iii)to evaluate immune/inflammatory status:a.in the gut: by dosing β-defensin 2, human neutrophil peptides HNP1-3, calprotectin (ELISA) and SCFAs (gas liquid chromatography)b.in plasma: by dosing plasmatic cytokines (Luminex), C-reactive protein (CRP) (ELISA) and immune cell phenotyping (flow cytometry)c.in the lung: by immune cell phenotyping (flow cytometry) and characterisation of immune infiltrate in lung tumour biopsies obtained during the operation (by immunohistochemistry).

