**Figure 1 F1:**
[figure not shown]
Study flowchart. BALF = broncho-alveolar lavage fluid, CT = chemotherapy, D = day, Pchir = the group of patients undergoing surgery, Pct-chir = the group of patients undergoing chemotherapy and surgery. ^∗^performed as a part of patient's standard medical care if decided by his/her physician.

As presented in Figure 1, group Pchir has sampling concentrated around 1 event—surgery. At hospital admission (D-1 before surgery), samples of saliva, blood and faeces are collected together with the nutritional survey patients made during the preceding week (D-7 to D-1). The BALF and lung tissue samples are collected during the surgery (D0) from the excised lobe.

Group Pct-chir (Fig. 1) has sampling concentrated around 3 events:

i)1st chemotherapy cycle (CT1)—the day of CT1, samples of saliva, blood and faeces are collected together with nutritional surveys patients made during the preceding week (same as D-1 for Pchir group). After sample retrieval, patients continue with their medical care procedure. Optionally, in the days preceding the CT1 as the part of their standard medical care, patients can undergo bronchoscopy. In this case, a part of retrieved liquid (BALF) is taken for microbiota characterisation and immune cell profiling.ii)2nd chemotherapy cycle (CT2) —CT2 is usually 3 weeks after CT1. The day of CT2, only saliva, faeces, and nutritional surveys are retrieved. After sample retrieval, patients continue with their medical treatment.iii)Surgery—The time elapsed between CT2 and surgery is about 1 month, depending on the patient's overall health status. The sampling for surgery is exactly the same as for group Pchir. At hospital admission (D-1 before surgery), samples of saliva, blood and faeces are collected together with nutritional surveys patients made during the preceding week (D-7 to D-1). The BALF and lung tissue samples are collected during the surgery (D0) from the excised lobe.

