The strong point of this trial is that study participation does not modify the patient's standard care treatment in any way. Invasive intervention, such as sampling of the lung tissue, is done during operation on the lung already removed from the patient. The BALF sampling during operation is performed directly on the dissected lobe, posing no additional inconvenience for the patient and drastically minimising UAs contamination, which is an important advantage to this study's concept. Likewise, sampling of the BALF at CT1 for group Pct-chir is done in the scope of a standard care procedure by bronchoscopy and it is not imposed by the study. However, the latter is also an inconvenience because there will be patients from group Pct-chir who will not undergo bronchoscopy with BALF sampling since it is not prescribed by his/her physician. Another thing to consider is also the difference in sampling technique of BALF. Sampling of BALF at CT1 for group Pct-chir is done by bronchoscopy, while sampling during surgery is done directly on the excised lobe for both groups. Therefore, the 1t BALF has a higher risk of contamination by UAs, while the 2nd BALF (during operation) should have no UAs contamination and better represent luminal microbiota specific of the tumour lobe. This will be taken into account during data interpretation, and if necessary, each time point will be characterised for itself.

In conclusion, in the group Pct-chir, the effect of chemotherapy on the microbiota of saliva and faeces and immune parameters of blood and faeces will by systematically assessed. Chemotherapy's effect on immune parameters and microbiota in BALF will be assessed only if obtained data in quantity and quality will permit it (as explained above). When talking of lung tissue, “healthy” lung tissue, taken at distance from the tumour, will be considered as a control^[12]^ tissue for comparison with peritumoural and tumoural tissue, as well as with BALF. Also, characterisation will be done respective to the tumour type where possible (sufficient patient number with the same tumour type).

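### Surgical BALF is defined as tumour-lobe fluid, but the sampling procedure covers whole-lung specimens with no step restricting the lavage to that lobe

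*Protocol article*

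**What the plan says.** The definition is in section 2.2 (Study outcomes). "As its primary outcome, this study will characterise the lung and UAs microbiota in 2 groups of 20 patients with NSCLC", and one of the lung samples listed there is "broncho-alveolar lavage fluid (BALF) from the tumour's proximity (same lobe".

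Section 2.5 (Trial design and timeline) keeps to the lobe. For both groups, "The BALF and lung tissue samples are collected during the surgery (D0) from the excised lobe". It adds that "The BALF sampling during operation is performed directly on the dissected lobe", and that this fluid should "better represent luminal microbiota specific of the tumour lobe". Section 5.2 claims novelty for lavage done on the tumour lobe without passing through the upper airways.

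The procedure is in section 3.5 (Lung tissue and BALF). It opens with "Sampling of lung tissue and BALF during surgery is performed for both groups, after partial or complete pneumonectomy". The tumour is located by palpation and a wedge of healthy lung is clamped off. Then "The stich on the bronchus is cut away and using a sterile syringe the lung is inflated through the bronchus". Two instillations of 40 mL follow, and 8–10 mL is recovered in total. The volume does not depend on how much lung was removed.

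**The concern.** The definition and the procedure cover different specimens. A lobe-level definition fits a removed lobe. Section 3.5 also admits a whole removed lung, and nothing in its steps turns a whole-lung lavage into a tumour-lobe one. If the stump that is opened leads to more than one lobe, the recovered fluid can contain material from lobes without tumour.

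What is at stake is the meaning of one primary-outcome sample. Section 2.5 plans to compare healthy lung tissue with peritumoural tissue, tumour and BALF, and section 2.2 lists concordance of genera between sample locations. Fluid from other lobes would weaken any feature peculiar to the tumour's lobe in those comparisons. Section 2.5 already accepts that lavage technique changes what BALF represents: it contrasts bronchoscopic with surgical BALF and undertakes to allow for the difference. It gives no similar warning for resection extent and treats surgical BALF as uniform.

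**Working it through.** The article gives no figure to reproduce, so the check is mainly a comparison of sections.

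| Question | Sections 2.2, 2.5, 5.2 | Section 3.5 |
|---|---|---|
| Unit sampled | The tumour's lobe (2.2); the removed lobe (2.5); the tumour lobe (5.2) | Lung removed by partial or complete pneumonectomy |
| Route | Lavage on the lobe itself | Through the bronchus once its stitch is cut away; not said whether main or lobar |
| Part kept out of the lavage | Not addressed | Only the clamped wedge of healthy lung |
| Use made of tumour position | Defines the sample | Found by palpation, but no step uses it to direct the lavage |
| Volume | Not addressed | 2 × 40 mL for every specimen |

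Step 1. For a one-lobe specimen the two columns agree: the opened bronchus serves the removed lobe, and 2.2 is met.

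Step 2. For a whole-lung specimen they need not agree. Someone following 3.5 as written would have done everything it asks, yet could hold fluid that does not meet 2.2.

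Step 3. The number of patients concerned cannot be derived, because the article does not give the share of complete pneumonectomies. For illustration, with 40 planned patients and an assumed share p, the count is 40 × p:

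- p = 0.05: 40 × 0.05 = 2
- p = 0.10: 40 × 0.10 = 4
- p = 0.20: 40 × 0.20 = 8

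A share of zero is equally compatible with the text.

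Step 4. Possible dilution, also on assumptions. Suppose the lavage reaches L lobes and each contributes equally. Let d be the amount by which a relative abundance in the tumour's lobe departs from that in the other lobes. One such sample then shows d/L, which is 0.50d for L = 2 and 0.33d for L = 3. Averaged over all patients, the visible departure is [1 − p(1 − 1/L)]d:

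- p = 0.05, L = 2: 1 − 0.05 × 0.50 = 0.975, so 0.975d
- p = 0.20, L = 3: 1 − 0.20 × 0.667 = 0.867, so 0.867d

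An affected sample could therefore lose a good deal, while the average over the series would move little unless whole-lung resections are common. This scaling suits relative abundances at best. It does not carry over to alpha diversity or to the distance-based tests in section 4.7.1.

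**The case against.** The strongest reply is that the lobe instruction already exists. Sections 2.2 and 2.5 name the lobe, 3.5 has the tumour located before the lavage begins, and 3.5 may simply be carrying out what was said earlier. How an uncommon specimen is cannulated could be specified in the full protocol, which is not shown. Part of this stands: the absence of an analysis term for specimen type is not a fault in an article. It does not remove the mismatch. Section 3.5 is a bench-level procedure, down to clamp order and tube size, and it names complete pneumonectomy expressly. Its steps and the definition in 2.2 need to agree.

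A reader might go further and infer that the procedure lavages the whole specimen and mixes lobes in every pneumonectomy patient. The article does not support that. It says "using a sterile syringe the lung is inflated through the bronchus" without saying which bronchus, it keeps a clamped wedge out, and it does not show that any enrolled patient had a whole lung removed.

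A reader might also infer an artefactual difference between Pchir and Pct-chir. That would need resection extent to differ by group, and the article does not say it does. Even at an assumed 5% against 15%, the arithmetic gives (0.15 − 0.05) × (1 − 1/L) × d, or 0.05d to 0.07d. Section 4.8.1 already calls the with/without-chemotherapy analysis descriptive only, although 4.8.6 lists unpaired tests.

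Nor is the main stated advantage of ex vivo lavage undermined. Section 2.5 names reduced upper-airway contamination, and that holds for a whole lung too. The three tissue samples in the primary outcome do not depend on the lavage route.

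**Conclusion.** The point holds in a limited form. Sections 2.2, 2.5 and 5.2 treat surgical BALF as a tumour-lobe sample. Section 3.5 applies one lavage to partial and complete pneumonectomy specimens without restricting it to that lobe. In whole-lung specimens the BALF may therefore not be lobe-specific, and the planned comparisons with tumour, peritumoural and healthy tissue could be diluted.

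The inconsistency rests on the wording alone. Its practical size rests on two things the article does not give: how many patients have a complete pneumonectomy, and which bronchus is used when they do. If there are none, or if a lobar bronchus is always used, the data are unaffected and only the text needs aligning. The shares and dilution factors above are illustrations, not estimates.

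**What to change.** 1. In section 3.5, state that the ex vivo lavage of a whole-lung specimen is limited to the tumour's lobe, for any specimens still to be collected, so that the sample meets 2.2.
2. Record resection extent for every patient.
3. Flag BALF already taken from whole-lung specimens as not confirmed tumour-lobe.
4. Repeat the BALF analyses without the flagged samples and report them beside the main results. If there are no such specimens, one sentence saying so closes the matter.

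The cost is one procedural sentence, one recorded variable and one repeated analysis. The lavage is done on tissue already removed, so patient care does not change. There are two downsides. The sensitivity analysis will hold slightly fewer BALF samples. And because recruitment runs from May 2017 to May 2019, with publication planned for early 2019, a revised step may reach few specimens and could introduce a technique difference between earlier and later whole-lung lavages. The flag identifies the earlier ones, so that difference can be seen and examined.

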## Methods and analyses

4

Saliva, “healthy” lung, peritumoural, and tumour tissue, BALF and faecal samples will be used for bacterial DNA extraction, followed by qPCR and 16S rRNA gene sequence analysis to establish microbial profiles. Fresh faeces samples will be used for bacterial culture, and frozen aliquots for dosage of faecal calprotectin, β-defensin 2, HNP1-3 (ELISA), and SCFAs (gas liquid chromatography). The BALF and plasma samples will both be analysed by flow cytometry (immune cell phenotyping), while plasma will also be used for cytokines (Luminex) and CRP (ELISA) dosage. Tumour tissue stored in paraffin will be used for the analysis of immune infiltrate by immunohistochemistry. Each procedure is explained in detail in the following sections.

### Nutritional status

4.1

Nutritional data for each patient will be analysed using the Nutrilog 2.3 software package, a computerised database (Proform) that calculates food composition from the French standard reference.^[23]^

### Cytokines

4.2

Stored plasma will be analysed for cytokines corresponding (but not restricted) to the following profiles: Th1, Th2, Th17, Treg. Samples will be analysed using Luminex kits: HSTCMAG-28SK, HTH17MAG-14K and TGFBMAG-64K-01 (Merck Millipore). Analyses will be conducted by the phenotyping service of CREFRE, Toulouse, France.

### Evaluation of tumour immune infiltrate

4.3

Immunohistochemistry will be performed on tumour tissue using the specific antibodies to detect subpopulations of immune cells as follows: cytotoxic T-lymphocytes (anti-CD8, clone SP16, ThermoFisher Scientific), regulatory T-lymphocytes (anti-FoxP3, clone SP97, ThermoFisher Scientific), B-lymphocytes (anti-CD20, clone SP32, Cell Marque). The immune response checkpoint axis PD-1–PD-L1 will be assessed by anti-PD-1 (clone NAT105, Cell Marque) and anti-PD-L1 (clone 28-8, Abcam). All staining will be performed by a fully automated, standardised procedure (Benchmark XT, Ventana/Roche). The number of lymphoid cells expressing each antigen, except PD-L1, will be determined within 5 consecutive x40 microscopic fields, starting from the invasive front toward the tumour centre, used as a parameter reflecting the tumour's quantity of a given immune cell subpopulation. PD-L1 will be assessed for both immune and tumour cells and reported as the percentage of each population expressing the antigen.

### Immune cell phenotyping

4.4

Immune cell phenotyping will be performed on fresh samples of blood (0.5 mL) and BALF (3 mL) by flow cytometry. Leukocytes will be obtained after haemolysis (solution of 155 mM NH_4_Cl, 12 mM NaHCO_3_, 0.1 mM EDTA) for 15 min at room temperature, followed by 10 min centrifugation at 600 × g. Before centrifugation, BALF will be filtered through a porous gauze to eliminate mucus and reduce the viscosity. Lymphocyte subpopulations will be phenotyped using the following antibodies: anti-CD3-VioBlue, anti-CD4-APC-Vio770, anti-CD25-APC, anti-CD127-VioBright FITC, anti-CD183 (CXCR3)-PE-Vio770, anti-CD294 (CRTH2)-PE, anti-CD196 (CCR6)-PE-Vio615, anti-CD15-FITC, anti-CD62L-PE, anti-CD11b-PE-Vio770 and Viobility 405/520 fixable dye, all purchased from Miltenyi Biotec. A T lymphocytes CD4^+^ will be characterised as CD3^+^CD4^+^ cells. Subpopulations of T lymphocytes CD4^+^ will be characterised as follows: Th1 as CD3^+^CD4^+^CD183^+^, Th2 as CD3^+^CD4^+^CD294^+^, Th17 as CD3^+^CD4^+^CD196^+^, Treg as CD3^+^CD25^+^CD127^-^ and neutrophils as CD15^+^CD11b^+^CD62L^+^/ CD15^+^CD11b^-^CD62L^+^ for “tethering” form, and CD15^+^CD11b^+^CD62L^-^ for active form. Due to high debris background in BALF samples, utilisation of the Viability dye is essential and utilisation of intracellular dyes is excluded. The data will be acquired using LSRII, BD Biosciences.

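### Section 4.4 lists Treg among the CD4+ T-cell subsets but defines it without CD4, so the written definition admits CD4-negative T cells

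*Protocol article*

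**What the plan says.** Section 4.4 (Immune cell phenotyping) first fixes the parent population: "A T lymphocytes CD4^+^ will be characterised as CD3^+^CD4^+^ cells". It then opens the list of subsets with "Subpopulations of T lymphocytes CD4^+^ will be characterised as follows". The first two definitions are "Th1 as CD3^+^CD4^+^CD183^+^, Th2 as CD3^+^CD4^+^CD294" (positive), and the next two are "Th17 as CD3^+^CD4^+^CD196^+^, Treg as CD3^+^CD25^+^CD127" (negative). The same sentence goes on to a population that is not a T cell at all: "and neutrophils as CD15^+^CD11b^+^CD62L^+^/ CD15^+^CD11b^-^CD62L" (positive).

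The antibody panel in that section includes "anti-CD3-VioBlue, anti-CD4-APC-Vio770, anti-CD25-APC, anti-CD127-VioBright FITC". It lists no anti-CD8. The section also rules out intracellular dyes, giving the debris in BALF as the reason.

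Section 2.2 makes flow phenotyping part of secondary outcome iii, in blood (item b) and "in the lung: by immune cell phenotyping (flow cytometry") (item c). Section 2.5 plans a systematic assessment of the chemotherapy effect on blood immune parameters in the Pct-chir group, with blood drawn at the first chemotherapy cycle and at admission for surgery. The same assessment in BALF is conditional on the data. Section 5.3 intends to relate BALF lymphocyte composition to the microbiota.

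**The concern.** The Treg definition disagrees with the population it is said to belong to. Three of the four T-cell subsets carry CD3+CD4+. Treg carries only CD3+, and then CD25+ and CD127-. A laboratory that follows the marker string and a laboratory that follows the opening words of the sentence would report different numbers from the same tube.

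If the string is followed, the Treg figure mixes two sources: CD4+ cells of the intended phenotype, and CD4-negative T cells that happen to be CD25+CD127-. The second source grows or shrinks with the share of T cells that are CD4-negative. A change in that share between the first chemotherapy cycle and surgery, or a difference in it between patients, could then be read as a Treg change or could mask one.

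Nothing else in the flow assay would catch this. Without intracellular staining there is no FoxP3 in blood or BALF. The FoxP3 staining in section 4.3 is immunohistochemistry on tumour tissue and cannot check the other two compartments.

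**Working it through.** The plan states no figure to reproduce here. The check has two parts: what the written definitions admit, and what the size of the error would depend on.

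**1. What the definitions admit.** Take a CD3+ cell and the six markers used in the T-cell definitions: CD4, CD183, CD294, CD196, CD25 and CD127. Each is positive or negative, so there are 2^6 = 64 patterns. These are counts of marker patterns, not of cells.

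| Definition | Markers fixed | Patterns admitted | Of these, CD4-negative |
|---|---|---|---|
| Th1, Th2 or Th17 (each) | CD4+ and one other | 2^4 = 16 | 0 |
| Treg as written | CD25+, CD127- | 2^4 = 16 | 2^3 = 8 |
| Treg with CD4+ added | CD4+, CD25+, CD127- | 2^3 = 8 | 0 |

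Half of the patterns admitted by the written Treg definition are CD4-negative. The helper definitions admit none. Adding CD4+ removes all eight.

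**2. What the size depends on.** Let p be the CD4+ share of T cells, t the fraction of CD4+ T cells that are CD25+CD127-, and r the same fraction among CD4-negative T cells.

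- Intended Treg, per T cell: p × t
- Treg as written, per T cell: p × t + (1 − p) × r
- Relative excess: (1 − p) × r / (p × t)

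The document gives none of p, t or r, so the excess cannot be computed. If r is zero, the two definitions agree. The following values are **assumptions chosen only to show sensitivity**: p = 60%, t = 6%. Per 100 T cells the intended count is 60 × 0.06 = 3.6.

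- r = 1%: 40 × 0.01 = 0.4; excess 0.4/3.6 = 11%
- r = 3%: 40 × 0.03 = 1.2; excess 1.2/3.6 = 33%
- r = 5%: 40 × 0.05 = 2.0; excess 2.0/3.6 = 56%

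Now keep t = 6% and r = 3%, and let p move from 60% to 45%. The written definition gives 3.6 + 1.2 = 4.8 before and 45 × 0.06 + 55 × 0.03 = 2.7 + 1.65 = 4.35 after.

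| Reported as | Intended definition | Written definition |
|---|---|---|
| Share of all T cells | 3.6% to 2.7% (25% fall) | 4.8% to 4.35% (9% fall) |
| Per CD4+ cell | 6.0% to 6.0% (no change) | 4.8/60 = 8.0% to 4.35/45 = 9.7% (21% rise) |

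Under these assumptions the apparent change differs from the intended one on either denominator, but its direction depends on which denominator is used, and section 4.4 names none.

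**The case against.** The strongest reply is that the omission is shorthand. The opening words of the sentence place Treg among CD4+ T lymphocytes, those are defined just before as CD3+CD4+, and anti-CD4 is in the panel. Read that way, Treg is already CD3+CD4+CD25+CD127-. Neutrophils share the sentence, but nobody would take them for T cells, whereas Treg stands beside the three helper subsets. This is also a condensed article, and a full gating hierarchy may sit in the full protocol.

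Part of this stands. A slip in the text is plausible, and the document does not show that any sample has been read without CD4. But the opening words cannot be relied on to supply the missing marker. The authors wrote CD4+ out three times in the same sentence and left it out once, and the sentence demonstrably covers a population that is not CD4+. The point is also not a missing detail: the article does state a definition, and that definition conflicts with its own parent population.

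A reader might infer four stronger things, none of which the document supports:

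- *That CD8 cells are being counted as Treg.* The written rule permits CD4-negative cells. It does not establish that they are counted.
- *That CD8 cells enter the helper subsets.* A CD4-negative cell cannot, because Th1, Th2 and Th17 all require CD4+.
- *That the subsets must be mutually exclusive.* They do overlap as written: each pair of helper subsets shares 2^3 = 8 patterns, and Treg shares 2^2 = 4 with each of them, a number that adding CD4+ to Treg leaves unchanged. But the document never says that the subsets are exclusive or sum to a total, and no analysis in section 4.8 needs them to be.
- *That the blood and BALF immune outcomes as a whole are wrong.* Total CD4+ T cells, the helper subsets, neutrophil forms, plasma cytokines, CRP and the tumour immunohistochemistry do not use the Treg string.

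**Conclusion.** The inconsistency is real and can be seen within one sentence of section 4.4. Taken literally, the Treg definition admits CD4-negative T cells, and the resulting count would partly track the CD4+ to CD4-negative balance in blood and BALF.

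The percentages in the check rest on assumed frequencies and an assumed denominator. They show that the readout could be sensitive to the omission and do not estimate the error.

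The reach is narrow. Only the Treg flow readout is touched, within secondary outcome iii. The primary outcome in section 2.2 is lung and upper-airway microbiota, and section 4.8.1 calls the study exploratory. The correlation analyses in sections 4.8.7 and 4.8.8 name cytokines and tumour infiltrate rather than blood flow subsets. Severity is minor to moderate: minor if the laboratory already reads Treg within CD4+ cells and only the text is wrong, moderate if the string has been applied as printed.

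**What to change.** In section 4.4, define Treg as CD3+CD4+CD25+CD127-, in line with the other three subsets and with the population announced for the list. Apply that single definition to every blood and BALF sample, at all time points and in both groups. Check how samples already acquired were analysed, and re-analyse the stored files for any that were read without CD4. Ideally this is done before the intermediary analysis that section 2.5 plans once half the patients (n = 20) have complete samples, and otherwise before the final analysis.

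The cost is one marker in the text and in the analysis template, plus re-analysis time where needed. Anti-CD4 is already in the panel, so no antibody, sample or patient is added. Re-analysis assumes that the acquired cytometer files were kept. The number of events in the Treg count may fall somewhat, which could matter most in BALF.
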